### Assignment of interventions: allocation

#### Sequence generation {16a}

Participants are randomly assigned to either intervention or 12-week waitlist (1:1), in clusters of 6, stratified by participant age to avoid > 4-year age gaps between participants in the intervention groups. Each site requests a randomization number when the site has ~ 6 consenting participants within each age range. A pre-generated randomization indicates whether the cluster will be either intervention or waitlist. The allocation sequence was computer-generated by a research coordinator who is independent of the PI. The sites and participants are advised of their allocation approximately 2 weeks prior to group dates, to respect their time management needs (e.g., planning time off school and work for participants; allowing time for other clients for group leaders). Participants allocated to waitlist receive the intervention after 12 weeks. The dates for the potential waitlist groups are included in the original invitation letter to ease families’ planning.

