Across sites, the general procedure principle is that each site coordinator contacts the central project coordinator when they have at least 5 consenting participants. For each intervention group, 3–8 consenting families are required to allocate a randomization number. Participants receive all pre-intervention questionnaires approximately 1 month before the set group date, with regular reminders if not completed. Approximately 2 weeks before the set group date, families and group leaders are informed by the central research coordinator about whether the group was allocated to intervention or waitlist. If assigned to waitlist, participants receive the baseline questionnaires again 2 weeks before the intervention date (approximately 12 weeks after the initial group date). The aim is to conduct 48 groups over the project period. We have pre-generated a randomization list with 100 numbers, ensuring that there will never be more than 3 allocations to the same arm in a row (i.e., intervention or waitlist). This way, the number of participants in both arms will be somewhat balanced if we have to end the trial before reaching our aim of 48 groups, or if we need to increase the number of groups due to < 6 families per group (the aim is 288 families, i.e., 6 × 48).

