#### Plans to promote participant retention and complete follow-up {18b}

Reminders are sent to all participants at each measurement point, via SMS and/or email, depending on participants’ preferences. To collect as much data as possible, a backup electronic version of only the main outcome (SDQ) is offered to participants who do not complete the full questionnaire passages at each measurement point. In cases where participants have not completed the pre-intervention questionnaire before the first group session, time is set apart for the family to complete the main outcome on site.

Newsletters from the project are published twice yearly on the study website (www.sibs.no) to keep participants informed about the study. All analyses will be done with treatment completers as well as the intent-to-treat sample.

See the “Recruitment {15}” section for further details regarding the retention and follow-up plans.

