### Statistical methods

#### Statistical methods for primary and secondary outcomes {20a}

The main effect is measured as the difference between the intervention group and the waitlist group in SDQ scores from pre-intervention to 3 months, reported by siblings, parents, and teachers. This is investigated using mixed ANOVA, and effect sizes will be reported as Cohen’s *d*. To examine the effects beyond waitlist for the complete sample, we apply growth curve modeling, which enables us to investigate both mean changes at a group level over time and individual growth trajectories, with the inclusion of individuals with partial/missing data [26]. A series of linear mixed models are fitted. A model with only fixed and random intercepts serves as the null model, to which subsequent unconditional models of time will be compared. Finally, group membership and control variables are included in a set of conditional models, through which the longitudinal effect of the intervention is investigated. Growth curve models are fitted separately for the intent-to-treat sample and per-protocol, excluding participants with concomitant sibling care during follow-up. Multilevel analyses controlling for nesting (group and site level) are conducted with MPlus. Other analyses are conducted using updated versions of IBM SPSS and R.

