## Discussion

SIBS-RCT started participant recruitment and inclusion in September 2019. Recruitment is going according to plan, but many participants need several reminders before completing the online questionnaires. We believe this reflects the strain families of children with ND live under. We developed shorter versions of the questionnaire package to ensure we get as much data as possible on the main outcome variable, the SDQ.

SIBS-RCT corresponds to a societal need, in that Norwegian legislation requires health personnel to address the needs of siblings. Yet, ND and its impact on families represent a global challenge. We have tried the SIBS intervention with 54 families in Cambodia, with promising results on mental health, but not on family communication (submitted). Work is underway to adapt the manual further to the Cambodian culture. The team behind this proposal is interested in further international collaborations, and all materials are translated into English. For requests about implementation, contact the first or last author.

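### Allocation is disclosed whether or not the baseline SDQ is in, so late baselines are rated with the arm known, and only the intervention arm can complete them on site

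*Protocol article*

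**What the plan says.** All references are to the protocol article.

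- **Dispatch of baseline** (Implementation {16c}): "Participants receive all pre-intervention questionnaires approximately 1 month before the set group date, with regular reminders if not completed".
- **Disclosure** (same section): "Approximately 2 weeks before the set group date, families and group leaders are informed by the central research coordinator" of the group's arm. Sequence generation {16a} gives the same lead time and explains it by the planning needs of families and group leaders. Neither section makes disclosure depend on a completed baseline.
- **Fallback for late families** (section {18b}): "In cases where participants have not completed the pre-intervention questionnaire before the first group session, time is set apart for the family" to fill in the main outcome, the SDQ, at the venue. The same section offers an SDQ-only backup form at every measurement point.
- **Waitlist arm**: "Participants allocated to waitlist receive the intervention after 12 weeks" (Sequence generation {16a}), and "If assigned to waitlist, participants receive the baseline questionnaires again 2 weeks before the intervention date (approximately 12 weeks after the initial group date") (Implementation {16c}).
- **Primary contrast** (Statistical methods {20a}): "The main effect is measured as the difference between the intervention group and the waitlist group in SDQ scores from pre-intervention to 3 months", rated by siblings, parents and teachers and analysed by mixed ANOVA.
- **Masking** (section {17a}): none.
- **Experience so far** (Discussion): "many participants need several reminders before completing the online questionnaires".

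**The concern.** A baseline protects a change analysis only if it is measured without knowledge of the arm, or at least under the same conditions in both arms. Here a late family rates its baseline after being told its allocation. An intervention family may do so at the venue, minutes before treatment starts. A waitlist family can only do so remotely, knowing that it has to wait. Nobody is masked and the SDQ is a subjective rating, so either situation could move the answers.

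Two things are at stake. First, the baseline is one of the two terms in the change score, so a shift that differs between arms passes straight into the primary estimate. Second, a conventional mixed ANOVA needs both time points. A last-chance rescue of baselines that exists in one arm only can make inclusion in the primary analysis depend on the arm. The section on missing data {20c} assigns partial data to the growth curve models, not to the ANOVA.

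**Working it through.** The point disputes none of the plan's figures. The check is a timeline, followed by an illustration of size.

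**Timeline** (initial group date = week 0; all times approximate)

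| Week | Intervention arm | Waitlist arm |
|---|---|---|
| -4 | Baseline forms sent | Baseline forms sent |
| -2 | Allocation disclosed | Allocation disclosed |
| -2 to 0 | Late online baseline: arm known | Late online baseline: arm known |
| 0 | First session; on-site SDQ possible, counts as baseline | No session; no on-site SDQ possible |
| 10 | - | Baseline set sent again (12 - 2 = 10) |
| 12 | - | First session |

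Three things follow.

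1. About two weeks (4 - 2 = 2) are available to obtain a baseline before disclosure. Anything later is rated with the arm known, in both arms.
2. The on-site baseline at week 0 exists in the intervention arm only. This follows directly from {16a}, {16c} and {18b}.
3. Anything a waitlist family completes at its own first session is dated about week 12, some two weeks after the repeat forms went out. If the fallback applies there, it supplies a post-waitlist SDQ, which is the waitlist side of the primary contrast. This is an inference, because {18b} speaks of the pre-intervention form and does not mention the post-waitlist one.

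**Effect on the contrast**

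Contrast = (I_post - I_pre) - (W_pw - W_pre).

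Let a share f_I of intervention baselines be shifted by s_I, and a share f_W of waitlist baselines by s_W. The contrast then moves by

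-(f_I x s_I) + (f_W x s_W).

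Equal products cancel, and shifts in opposite directions add up. Only the difference between arms matters.

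**Illustration.** The article gives neither shares nor shifts, so these are assumptions, on the same SD scale as the planned effect of 0.4. With one arm affected (f_W x s_W = 0), the size of the movement is f x s:

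| Share | Shift (SD) | Movement (SD) | Relative to 0.4 |
|---|---|---|---|
| 0.10 | 0.1 | 0.01 | 2.5% |
| 0.20 | 0.2 | 0.04 | 10% |
| 0.30 | 0.3 | 0.09 | 22.5% |

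With 288 / 2 = 144 siblings per arm, shares of 10-30% are about 14 to 43 children.

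If the inferred waitlist route also operates, with the same share and a shift in the same direction, W_pw moves the contrast the same way as I_pre. The range doubles to 0.02-0.18 SD. This is an upper illustration that rests on a further assumption.

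**The case against.** Much of the case on the other side is sound.

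- **Both arms are told at the same time.** A reader might infer that the baseline can be shifted in the intervention arm only. The documents do not support that: a waitlist family that replies online in the last two weeks also knows its arm. Only the on-site setting is specific to one arm. The one-arm formula is an illustration, not an estimate.
- **The waitlist endpoint.** A reader might infer that the fallback definitely collects primary endpoints on site in the waitlist arm. The text does not say so. Knowing the arm is also no special defect there, because in an open trial every 12-week SDQ is rated with the arm known. The fallback could add only a different setting and a slightly later date.
- **Size.** Both inputs are assumed. The remark about reminders concerns online questionnaires in general and gives no share of late or on-site baselines. The mid-range value, 0.04 SD, is modest.
- **Mitigation.** The SDQ-only backup form is open to everyone, so on-site completion is a last resort. Teachers also rate the SDQ, and the on-site time is for families, so teacher ratings are probably untouched by that route. It would be too strong to say that nothing in the trial could reveal or limit the bias.
- **Full protocol.** Flagging of late forms and sensitivity analyses may be specified in the full protocol, which is available on request, or in an analysis plan. Their absence from the article is not counted here.

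What remains is the procedure that the article does fix: disclosure at a set time regardless of baseline status, followed by an on-site rescue at week 0 that one arm can use and the other cannot. An analysis plan cannot change when and where a rating was made.

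**Conclusion.** The concern holds for late self- and parent-rated baselines. Followed as written, the plan produces some baselines rated after disclosure in either arm, and some rated at the venue on the course day in the intervention arm alone. Any resulting difference between arms, in shift or in availability, enters the primary change contrast.

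Size and direction cannot be determined from the article. It would be tempting to conclude that the bias favours the intervention, but nothing in the text supports a sign. Under the stated assumptions, with one arm affected, the movement is 0.01-0.09 SD, which is 2.5% to 22.5% of the 0.4 target. It is smaller if both arms shift alike and larger if they shift in opposite directions. The effect on the post-waitlist endpoint is a possibility that depends on how section {18b} is meant.

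The procedure should be tightened because the remedy is cheap and the primary outcome is affected. It does not by itself invalidate the trial.

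**What to change.** 1. **Collect before disclosure.** Use the existing SDQ-only backup form to obtain the baseline SDQ from families in both arms before the planned disclosure date, and close the baseline window on that date. Disclosure stays where it is, so families and group leaders keep their roughly two weeks' notice.
2. **Record** completion date and mode (online or on site) for every SDQ.
3. **Sensitivity analysis.** Set baselines completed after disclosure to missing in a likelihood-based mixed model, which keeps the child in the analysis. This should not be done inside the mixed ANOVA, which would drop those children. Where completion dates exist, the analysis can also cover families already enrolled.
4. **Clarify section {18b}.** State whether the on-site fallback applies at the waitlist arm's first session. If it does, flag those SDQs. Use the same collection window and mode for the 12-week SDQ in both arms.

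The cost is a small coordination burden at the sites and the central office, and some baselines missing in the sensitivity analysis (14 to 43 intervention siblings under the assumed 10-30%, fewer if step 1 works). The sample size and the main analysis do not change.

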**Methods:**

We are conducting a randomized controlled trial comparing a five-session manual-based group intervention for siblings (aged 8 to 16 years) and parents of children with neurodevelopmental disorders to a 12-week waitlist, called SIBS-RCT. The intervention comprises three separate sibling and parent group sessions and two joint sessions in which each sibling talks to their parent alone. The intervention aims at improving parent-child communication and covers themes such as siblings’ understanding of the neurodevelopmental disorder, siblings’ emotions, and perceived family challenges. Participants are recruited through municipal and specialist health centers across Norway. The primary outcome is sibling mental health. Quality of life and family communication are secondary outcomes. Participants are block-randomized to the intervention or 12-week waitlist in groups of six. Measures are collected electronically at pre- and post-intervention/waitlist, as well as 3, 6, and 12 months post-intervention. The main effect to be examined is the difference between the intervention and waitlist at 12 weeks post. All outcomes will also be examined using growth curve analyses. We plan to include 288 siblings and their parents by the end of 2022.

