#### Criteria for discontinuing or modifying allocated interventions {11b}

Because the intervention is conducted over two half days, there are no explicit criteria for discontinuing or modifying the intervention. If a family does not show up on the second course day, or do not submit questionnaires, we attempt to continue to collect data from these participants to examine trajectories of change based on partial data.

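### The treatment-completer version of the 12-week contrast selects on attendance that has happened in the intervention arm but cannot yet have happened in the waitlist arm

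*Protocol article*

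**What the plan says.** Section 18b of the protocol article (participant retention) commits to two analysis sets throughout: "All analyses will be done with treatment completers as well as the intent-to-treat sample". It does not define a completer for either arm or say which set is primary.

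The main effect falls within that commitment. The abstract says: "The main effect to be examined is the difference between the intervention and waitlist at 12 weeks post". Section 20a says: "The main effect is measured as the difference between the intervention group and the waitlist group in SDQ scores from pre-intervention to 3 months".

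The timing is set elsewhere. Section 16a: "Participants allocated to waitlist receive the intervention after 12 weeks". Section 16c: "If assigned to waitlist, participants receive the baseline questionnaires again 2 weeks before the intervention date". Section 11a puts the intervention on two days one week apart, and section 11b allows for families who miss the second.

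Sections 11d and 20a also describe a per-protocol set, but it excludes on concomitant care. It is a different filter from attendance.

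**The concern.** A completer analysis at least needs a completer to mean the same thing in both arms at the time of the comparison. Here the waitlist design rules that out at 12 weeks. Intervention families have shown by then whether they complete, and waitlist families have had nothing to complete.

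Attendance is plausibly related to prognosis. Section 15 expects strained families to have difficulty attending, and the Discussion links late questionnaires to the same strain. If families who do not complete differ in SDQ change from those who do, removing them from one arm shifts the contrast with no treatment effect present. The result would then be reported beside intent-to-treat on the trial's headline question, where a reader could take it as supporting evidence.

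**Working it through.** The plan gives no figure to reproduce here. The check is the order of events, followed by an illustration of size.

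**Order of events**

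| Event | Intervention arm | Waitlist arm |
|---|---|---|
| Own sessions | Initial group date, second day one week later | After the 12-week wait |
| SDQ for the main contrast | 12 weeks / 3 months, after both days | Sent about 2 weeks before own sessions |
| Completion status at that SDQ | Known | Cannot exist |

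Section 18b lets a family that is late with the pre-intervention questionnaire fill in the SDQ on site. Even if that extends to the waitlist arm, the SDQ still precedes the sessions.

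**What a completer filter can do**

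Let q be the share of an arm removed as non-completers. Let g be the gap in mean SDQ change, in SD units, between would-be completers and non-completers when treatment has no effect. The whole-arm mean is (1 − q) × completer mean + q × non-completer mean, so filtering shifts the arm by q × g.

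- *Waitlist arm unfiltered.* The bias in the contrast is q × g.
- *Waitlist arm filtered on its later attendance.* The bias is (q × g in the intervention arm) − (q × g in the waitlist arm). It cancels only if selection works identically in both arms. In the waitlist arm, attendance follows the 12-week SDQ and may depend on how the sibling is doing by then. In the intervention arm, attendance comes before it.

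**Illustration, waitlist arm unfiltered**

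The documents give neither q nor g. The upper value q = 0.27 is the sample-size section's combined allowance for dropout and concomitant care, used only as a ceiling. The other q values and all g values are assumptions. The 0.4 is the minimal relevant effect in the sample-size section.

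| q | g (SD) | Bias q × g | Bias / 0.4 | Two-sided error at nominal 5% |
|---|---|---|---|---|
| 0.10 | 0.3 | 0.030 | 7.5% | 5.5% |
| 0.20 | 0.3 | 0.060 | 15% | 6.7% |
| 0.20 | 0.5 | 0.100 | 25% | 9.8% |
| 0.27 | 0.5 | 0.135 | 34% | 13.5% |

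The last column takes 144 per arm (288 / 2) before filtering and the plan's inflation factor of 1 + 5 × 0.11 = 1.55. The standard error is √[1.55 × (1/(144(1 − q)) + 1/144)]. For q = 0.27 this is √[1.55 × (1/105.12 + 1/144)] = 0.160, so the shift is 0.135 / 0.160 = 0.85 standard errors. Reversing the sign of g reverses the bias and leaves the error rate unchanged.

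**The case against.** **Intent-to-treat is planned alongside.** This stands. The criticised sentence itself runs every analysis in the intent-to-treat sample, and nothing calls the completer result primary. A reader might infer that the trial's main result is biased, but the documents do not support that. The flaw is in a companion analysis.

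**Completer is undefined, and definitions are commonly left to the analysis plan.** This stands in part. The quantity q × g applies only if the waitlist arm is left unfiltered. But no definition gives a matching filter, because the waitlist arm's attendance always comes after its endpoint. The difficulty lies in applying the set to this contrast at all.

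**The size and direction are assumed.** This stands. Non-attendance is nowhere reported, and with only two half days it could be well below 27%. A reader might infer that dropping strained families must favour the intervention. The protocol links strain to difficulty attending and to slow response, but says nothing about SDQ change. Strained families could start higher and improve more, which would turn the bias the other way.

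**A further inference to avoid.** Section 11b reads "If a family does not show up on the second course day, or do not submit questionnaires, we attempt to continue to collect data". A reader might conclude that intervention families who attend neither day are not followed up. That section does not limit collection to the families it names. Section 18a keeps inviting anyone who misses a measurement point unless they withdraw, and section 18b sends reminders to all participants at every measurement point. No change to section 11b is needed.

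**Conclusion.** The point holds for one analysis: the completer version of the 12-week intervention-versus-waitlist contrast. It follows from the protocol's own timeline and does not depend on the illustrative figures. It assumes only that completion refers to attending the sessions, which is the ordinary meaning and fits section 11b.

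The size cannot be fixed from the documents. Under the stated assumptions it runs from negligible (0.03 SD) to about a third of the minimal relevant effect (0.135 SD), in an unknown direction. The intent-to-treat contrast is untouched. The post-intervention trajectories do not share the problem, because both arms have by then been offered the sessions. This should be corrected, but it does not threaten the trial's main comparison.

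**What to change.** 1. Name intent-to-treat as the primary analysis set for the 12-week contrast.
2. Replace the completer version of that contrast with a complier-average estimate in all randomised siblings. Use allocation as the instrument and attendance at any session as the exposure, and allow for clustering by group. Waitlist families have no access before their 12-week SDQ, so non-compliance is one-sided by design. The method also assumes that allocation alone does not change the SDQ in families who attend neither day. The protocol should state this, since nobody is blinded.
3. Keep completer-only results for the post-intervention trajectories.

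Any attendance is preferable to the proportion of sessions attended, which would add a linear dose assumption.

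**Cost.** Protocol wording, an attendance record for each family from the sites, and one extra model. The interval widens. Suppose the share attending neither day were as large as the q values above. The complier-average standard error is about √(2/144) / (1 − q), against √[1/(144(1 − q)) + 1/144] for the naive completer contrast; the inflation factor multiplies both. At q = 0.10 this is 0.131 against 0.121 (8% wider). At q = 0.27 it is 0.161 against 0.128 (26% wider). Families who attend one day count as exposed, so the actual widening should be smaller.
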